### Data safety and monitoring

2.6

The data will be kept safe with the principal investigator (PI) and later with the data manager on a separate hard disk and local server (password protector) with the access to the same being provided to stakeholders only on a need to share basis.

### Data confidentiality

2.7

All the information collected will be stored only with the investigators and the data manager. The publications will not reveal any private information of any of the participants. If any qualitative aspect is added at a later stage (like a case study), it will only be done with the participant's consent.

As of now we are not planning on collecting any confidential data which might be harmful for the participants.

## Discussion

3

This trial will evaluate the use of health worker training as a tool for improving the clinical competence in relation to type 2 diabetes mellitus. We anticipate that the module will provide a greater understanding of type 2 diabetes mellitus, the importance of screening of both disease and complications and improved skills for the same.

Though many studies have focused on health worker training in the high-income nations, there is a dearth of evidence about a competence focused training package for health workers in type 2 diabetes mellitus in low- and middle-income countries like India. The findings of the study can serve as a cornerstone for training policies for health workers. It may help in reducing the cost burden of type 2 diabetes mellitus management on the public sector and the persons living with diabetes mellitus but more research on the impact of such a study will be needed to be undertaken for realizing the same. The results of the study will be disseminated by publishing them in peer reviewed journals.

### Strengths

3.1

The principal merit of the study is that it is one of a kind. It will help develop a standardized training and evaluation, competence package for health workers, specific to type 2 diabetes mellitus. Very few studies have focused on the same.

### Limitations

3.2

The study is limited to one district of the country. Hence, local factors contributing to the study's success or failures might not be replicable in all states. Objective measurements are time and resource-consuming and hence subjective practical evaluations are being incorporated.

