### Study design

2.3

We will conduct a 12 months prospective, unblinded, parallel cluster randomized controlled trial. The study will measure changes in healthcare worker competence levels related to type 2 diabetes mellitus and complications. The health centers chosen as the clusters will be then randomized into intervention and control arms. The health workers at the respective health center will be thus assigned to the respective cluster arm. The clusters will be chosen such that they are geographically distinct. This will avoid any possible contamination within the groups. Health workers in the control group will continue to deliver services according to the current standards and guidelines.^[28,30,31,35]^ The intervention group participants will undergo additional training. This will be spread over six months and delivered for 20 hours.^[36]^ It will entail pre and post-assessment questionnaires and practical assessments as the modality of evaluation.

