#### Implementation of intervention

2.4.1

The implementation of the intervention package consists of training of health workers and evaluation of the training on the clinical competence of the health workers undergoing the training. The intervention will be implemented in the following manner:

1.Identification & Selection of health centers2.Needs assessment of important stakeholders to improve the efficacy of the subsequent training3.Development of Intervention package and its validation4.Identification & recruitment of health workers for study5.Delivery of Intervention package:a.Health worker Training: The first part of the package will focus on the training of the health workers in the intervention arm.b.Evaluation of training: The second part of the package will focus on the evaluation of the training. This will be done using the questionnaire tool developed for pre and post-session and pre and post-intervention evaluation of the theoretical competence. An additional practical evaluation will be conducted by a neutral doctor to assess that change in clinical competence. The evaluation mechanism will be identical in both the control and the intervention arms (Fig. 2 showcases the overview of the intervention).

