#### Training of health workers

2.4.2

The HWs in the intervention arm will then undergo the customized training. The training module will include the following topics^[3,28]^:

NCD's and their prevalence in rural areasImportance of prevention, early detection and managementDiabetes and its prevalence in India and rural IndiaDiabetes Pathogenesis,Signs and symptoms and basic pathology of diabetesCommon drugs used, Insulin,Importance of self-management,Key Skills- Using risk assessment tools, generating awareness history taking, behavior counselingScreening, Measurement of blood glucose (using glucometer)Complications-∘Hypoglycemia∘Wound and ulcers in diabetes∘Oral complication of diabetes∘Diabetic Foot∘Diabetic Nephropathy∘Diabetic Retinopathy, etc.Follow-up & its importance: Motivation for follow-up, Motivation & Support for lifestyle changes, community meetings, patient support groups, continuity of careIndian Health System and approach to primary care.

The module will be collated using the available modules which were developed and published by the Ministry of Health and Family Welfare, Government of India, Indian Council of Medical Research operational guidelines, The National Program for Prevention and Control of Cancer, Diabetes, Cardiovascular diseases and Stroke operational guidelines and literature from Indian Institute of Public Health-Hyderabad & Public Health Foundation of India.

After the 6-month training phase, an evaluation will occur. The evaluation will consist of theoretical and practical components which will be conducted using the developed questionnaire and the same set of trained public health experts respectively. The same tools would also be used for baseline collection. Both of these techniques will help assess the change in effective knowledge as well the practical skills about type 2 diabetes mellitus & associated complications. The detailed training plan is described below:

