#### Evaluation

2.4.3

The evaluation of the intervention package will help us understand the change in the competence of health workers in relation to type 2 diabetes mellitus and its complications. It will be conducted in the following manner for both the intervention & the control groups:

Paper basedOverall pre and post-test questionnaire, which will be derived from the diabetes knowledge test 2 of the Michigan University,^[33,34]^ the inputs from the physician/endocrinologist stakeholders, the assessment tools used by government training modules and evaluation tools developed by PHFI for diabetes training. This will help us understand the change in effective knowledge in the health workers in terms of type 2 diabetes mellitus, screening and complications.Practical BasedThis will be a practical test based on the training. It will help understand how effectively the training will be implemented by the health workers, when they are in contact with the diagnosed and undiagnosed patients. The scores of this assessment will be compared with the practical assessment carried out at the baseline.

Both the baseline and post training practical evaluation will be conducted by the same set of trained public health experts.

A combination of both paper-based and practical score will elucidate the change in the competence of the health workers.

Both the evaluation methods will be assessed according to objective parameters. It will ensure a comprehensive evaluation of all the components on which training will be provided (Table 1).

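### The protocol gives two accounts of who scores the practical test and of whether scoring is objective, and in an unblinded trial it does not say that these assessors are masked to arm

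*Protocol article*

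**What the plan says.** Four statements in the protocol article bear on how the practical test is scored.

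- **Who scores.** Section 2.4.1 (Implementation of intervention): "An additional practical evaluation will be conducted by a neutral doctor to assess that change in clinical competence". Section 2.4.3 (Evaluation): "Both the baseline and post training practical evaluation will be conducted by the same set of trained public health experts". Section 2.4.2 (Training of health workers) agrees with 2.4.3: the theoretical and practical parts will be "conducted using the developed questionnaire and the same set of trained public health experts respectively".
- **How it is scored.** Section 2.4.3: "Both the evaluation methods will be assessed according to objective parameters". Section 3.2 (Limitations): "Objective measurements are time and resource-consuming and hence subjective practical evaluations are being incorporated".
- **Blinding.** Section 2.3 (Study design): "We will conduct a 12 months prospective, unblinded, parallel cluster randomized controlled trial". No exception is made for outcome assessors.
- **Use of the score.** Section 2.4.3 combines the practical score with the paper score to show the change in competence, which is the aim of the trial. It gives no weights. Section 2.4.1 adds that both arms are evaluated by the same mechanism.

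**The concern.** These are conflicting statements about how part of the main outcome is measured, so they are more than detail left to a fuller document. A single doctor and a panel of experts are different assessors. A reader also cannot tell whether the practical mark follows set criteria or the examiner's judgement.

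The conflict matters because the trial is labelled unblinded. Whole health centres are allocated, so an assessor who knows the arm of a centre knows it for every worker there. If marks leave room for judgement, expecting trained workers to do better can raise their marks. That bias arises after allocation, so adjusting for the baseline score does not take it out. A larger sample does not help either: a smaller standard error makes a fixed bias more likely to reach significance. Workers and trainers cannot be masked to a training programme, but practical examiners can be.

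**Working it through.** **1. The passages side by side**

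| Question | One account | Other account |
|---|---|---|
| Assessor | a neutral doctor (2.4.1) | a set of public health experts, the same at both time points (2.4.2, 2.4.3) |
| Scoring | objective, for both methods (2.4.3) | subjective, for reasons of time and resource (3.2) |
| Masking of assessor | not stated; trial unblinded (2.3) | none |

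Neutrality suggests independence, and an identical mechanism standardises the procedure. Neither conceals the arm.

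**2. The plan's own sample size (section 2.3.2)**

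Inputs: z = 1.96 and 0.84, d = 0.5, cluster size m = 30, intracluster correlation 0.03, dropout 20%. The printed formula is missing from the text; the standard form fits.

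- Without clustering: 2 × (1.96 + 0.84)² / 0.5² = 62.72 per group
- Design effect: 1 + (30 − 1) × 0.03 = 1.87
- n = 62.72 × 1.87 = 117.3, stated as 117
- With dropout: 117 / 0.8 = 146.25, rounded up to 147; 2 × 147 = 294

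The stated figures reproduce, so no sample size error is involved.

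**3. What a rating bias would do**

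Standard error of the arm difference at 117 per group, in SD units: √(2 × 1.87 / 117) = 0.179.

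Let w be the weight of the practical score, r its correlation with the paper score, and b the extra mark given to trained workers, in SDs of the practical score. Then

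- SD of the combined score = √(w² + (1 − w)² + 2rw(1 − w))
- shift in the combined score = w × b / SD of the combined score

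The document gives none of w, r or b; all three are assumed. With w = 0.5 and r = 0.5 the combined SD is √(0.25 + 0.25 + 0.25) = 0.866. The true effect is set to zero. The t reference uses 8 clusters − 2 = 6 df.

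| b | Shift | Shift / 0.5 | Shift / SE | False positives, normal | False positives, t (6 df) |
|---|---|---|---|---|---|
| 0.2 SD | 0.5 × 0.2 / 0.866 = 0.115 SD | 23% | 0.65 | 9.9% | 8.5% |
| 0.4 SD | 0.5 × 0.4 / 0.866 = 0.231 SD | 46% | 1.29 | 25.3% | 19.4% |

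**4. Sensitivity to the assumptions**

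Over w from 0.25 to 0.75 and r from 0.3 to 1.0, the false-positive rate on the normal reference is about 6% to 16% at b = 0.2 SD and about 9% to 50% at b = 0.4 SD. On the t reference the ranges are about 6% to 13% and 8% to 38%. All exceed 5%.

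**5. What it would take to mimic the planned effect**

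With equal weights, a spurious difference of 0.5 SD needs b = 0.5 × 0.866 / 0.5 = 0.87 SD at r = 0.5, and 1.0 SD at r = 1.0.

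**The case against.** The case on the other side has several parts.

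- **Unblinded may describe only participants and trainers.** That is its natural meaning in a training trial, and a condensed article may leave assessor masking to the full protocol. This stands in part: the documents do not say that assessors are told the arm. But the label carries no exception, so masking can only be called not stated.
- **Objective and subjective may be reconcilable.** An examiner can rate performance against set criteria, and the tool is still to be developed and validated. That is possible, but 3.2 presents subjective evaluation as the alternative to objective measurement, so the wording still has to be reconciled.
- **The limitation is disclosed.** Disclosure neither resolves the conflict with 2.4.3 nor reduces a bias.
- **The sizes are assumed.** Correct; they are illustrations.

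A reader might also infer more than the text supports:

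- That half of the outcome is affected. There are two components, but no weights are given.
- That trainers may score their own trainees. No passage gives trainers the practical test; section 2.4.2 describes them as a separately selected group, and 2.4.1 calls the assessor neutral.
- That using the same examiners before and after is a fault. It is an ordinary consistency measure and does not by itself reveal allocation.
- That rating bias could produce the whole planned effect. At equal weights and r from 0.5 to 1.0 that needs about 0.87 to 1.0 SD, far above the 0.2 to 0.4 SD illustrated.

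**Conclusion.** Both contradictions stand in the current text, and masking of the practical assessors is not stated in a trial declared unblinded. Followed as written, the plan leaves the combined competence score open to a bias towards training that baseline adjustment would not correct.

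Whether such a bias will occur, and how large it would be, cannot be read from the document. The illustrated inflation of the false-positive rate, roughly two to five times the nominal 5% on the normal reference and somewhat less with t on 6 df, rests on equal weights, a correlation of 0.5, a rating bias of 0.2 to 0.4 SD and no true effect. The contradictions are certain; the bias is a possibility. The point should be settled before post-training scoring, because masking cannot be added afterwards.

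**What to change.** 1. Reconcile 2.4.1 with 2.4.2 and 2.4.3, so that one assessor group, among those already planned, conducts the practical test.
2. Reconcile 2.4.3 with 3.2: say whether marks follow a fixed item checklist, and use one for both arms at both time points.
3. State that these assessors are independent of the trainers and are not told centre allocation, that each scores workers from both arms, and that workers are asked not to disclose their training.
4. Amend 2.3 to participants and trainers unblinded, practical assessors masked. This is a design decision for the sponsor as well as a wording change.
5. Report the paper and practical scores separately as well as combined, so that a reader can see whether the result depends on the rated component.

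Cost: wording, and some rostering so that each assessor visits centres of both arms. No added staff. Masking may sometimes fail, since workers trained over six months may reveal it.
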